### **1.3 Standard evaluation of influenza vaccine response**

The rise in influenza-specific hemagglutinin inhibition (HI) antibody titers in pre- and post-vaccination serum is used as a measure of the immune response to the vaccine. Sero-protection in an individual is defined as a post-vaccination HI titer of ≥40. Seroconversion is defined as either a fourfold increase in HI antibody titer if the

pre-vaccination titer was  $\geq 10$  or a rise in HI titer from  $< 10$  to  $\geq 40$  following vaccination.

The Committee for Proprietary Medicinal Products (CPMP) have established criteria to determine whether the influenza vaccine is considered to elicit an effective overall immunogenic response in a population (25). According to these criteria, the influenza vaccine is considered effective if it meets one of the following three criteria: seroprotection in  $> 70\%$  of patients; seroconversion in  $> 40\%$  of patients; or a geometric mean fold increase (GMFI)  $> 2.5$ .

In the study by Kotecha *et al.*, the inactivated trivalent influenza vaccine containing the H3N2, H1N1 and B strains was considered to be immunologically effective by satisfying the criteria for a GMFI increase of  $> 2.5$  for all three vaccine strains. However, the vaccine did not meet efficacy criteria for seroprotection (H3N2 55%, H1N1 61% and B strain 41%) and seroconversion for the B strain (H3N2 43%, H1N1 43%, B strain 33%). In comparison, a recent multicentre open label study of inactivated monovalent H3N2 vaccine in healthy children aged 6 months to 17 years achieved seroprotection in 74% and 88% of children in the 3-8 year and 9-17 year old cohorts; while 72% and 85% seroconverted, respectively. In the same study, children aged 6 to 35 months showed a much lower response in general. Seroprotection and seroconversion were achieved in 19% and 38% of those that received one and two doses of the inactivated H3N2 vaccine, respectively. A group of children aged 6 to 35 months received one or two double doses of the vaccine (an equivalent of one or two standard doses for children  $\geq 3$  years old). These children achieved seroprotection and seroconversion in 30% and 47% of study participants, demonstrating an enhanced response (26). Overall, the data suggests room for improvement with regards to vaccine efficacy and identifying the ideal method with which to measure vaccine response in immunocompromised children with cancer.

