### **2.2.2 Secondary efficacy objectives**

- To define variables predictive of immune response to the inactivated influenza vaccine in a multivariate analysis of patient age, sex, type of diagnosis/treatment and parameters of base-line immune function including total lymphocyte count, B-cell count, CD4 and CD8 T-cell count, NK cell count, memory cells and immunoglobulin levels.
- To define the clinical incidence of laboratory proven influenza infection within the study population and determine whether infection correlates with cellular and humoral immune responses.

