### **3.7 Number of participants**

It is estimated that 80 subjects will be recruited over the study period. This is based on the incidence and prevalence of patients receiving diagnosis and treatment for cancer at Perth Children's Hospital Haematology and Oncology Department.

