### **5.2 Study interventions**

Each visit will comprise of two main components:

1. A blood sample will be taken to perform the following tests:
  - a. A full blood count (FBC) including the differential will be requested prior each vaccination. Vaccination will only proceed if absolute neutrophil count (ANC) is  $\geq 0.5 \times 10^9/L$ , as per the Australian Immunisation Handbook 10th Edition recommendations.
  - b. Lymphocyte subsets (prior Visit 1 only). This is to measure the number of B-cells, CD4 and CD8 positive T-cells, NK cells and memory T and B-cells.
  - c. IgG, IgA and IgM levels (prior Visit 1 only).
  - d. Cellular response to the influenza vaccine.

- e. HI antibody titer measurement.
- 2. Influenza vaccine will be given (with the exception of the exit visit) to the participant after a baseline medical check. Participants found to be physically unfit will have their vaccination postponed. A minimum 30 minute observation period will be provided to monitor for development of an acute adverse event (AE) to the vaccine.

Participant age, sex, primary oncological diagnosis and phase of treatment will be documented at the start of the study. A detailed medical history will be taken including history of previous influenza illness, influenza immunisation and allergy to egg.

A substantial effort will be made to schedule study visits to coincide with participants' regular follow up outpatient visits and appointments for chemotherapy. Where possible, blood samples will be obtained from accessed central venous access devices (CVAD) to spare participants from venepunctures solely for study purposes.

Study visits will be spaced by a minimum of 4 weeks and maximum of 6 weeks as per the Australian Immunisation Handbook 10th Edition recommendations regarding timing of influenza vaccination and to allow for flexibility in arranging suitable appointments for study participants.

Any AEs post influenza vaccination will be documented at each visit. Each participant's parent/guardian will also be contacted by telephone one week after the influenza vaccination to document any delayed AEs related to the influenza vaccine.

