### **9.3 Statistical analysis**

The primary immunogenicity endpoints will be the percentage of participants achieving seroprotection and seroconversion. To assess if the extra vaccination dose improves immunogenicity, a McNemar test will be used to assess the

difference in these percentages as calculated from the immunogenicity status obtained after the last two doses of each individual. We will also evaluate geometric mean titers of HI antibodies at baseline and after vaccination. The geometric mean fold increase (GMFI), with 95% confidence intervals, will be calculated for each strain, using a log-normal approximation for the distribution of HI antibody levels pre and post vaccination.

Multivariate logistic regression models will be used to assess the influence of clinically relevant demographic and immunological variables to predict seroconversion to each influenza vaccine strain and complete seroconversion to all strains of the vaccine. Linear regression analyses of log-transformed HI antibody titers and log-transformed T-lymphocyte IFN- $\gamma$  levels will be undertaken to assess the influence of clinically relevant variables on humoral and cellular responses to vaccination, respectively.

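### The predictor models put about 13–14 overlapping variables on at most 40 events, do not name baseline titre among them, and leave the outcome's dose unstated, so their findings are likely to be unreliable

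*Protocol*

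**What the plan says.** Section 9.3 plans that "Multivariate logistic regression models will be used to assess the influence of clinically relevant demographic and immunological variables to predict seroconversion", with one model per vaccine strain and one for seroconversion to every strain. It adds linear models of log HI titre and log IFN-γ.

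The candidates come from elsewhere. Section 2.2.2 sets the objective "in a multivariate analysis of patient age, sex, type of diagnosis/treatment and parameters of base-line immune function", and lists these parameters as "total lymphocyte count, B-cell count, CD4 and CD8 T-cell count, NK cell count, memory cells and immunoglobulin levels". Section 9.1 repeats essentially the same set. Section 5.2 shows what is measured: the subsets include "NK cells and memory T and B-cells", and the immunoglobulins are "IgG, IgA and IgM levels (prior Visit 1 only"). It also says "Participant age, sex, primary oncological diagnosis and phase of treatment will be documented at the start of the study".

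On sample size, section 3.7 says "It is estimated that 80 subjects will be recruited over the study period". Section 9.2 considers 60 and 80 participants, for the McNemar test only. Section 1.3 gives the earlier local results: "seroconversion for the B strain (H3N2 43%, H1N1 43%, B strain 33"%). It also defines seroconversion by reference to the pre-vaccination titre.

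Section 5.3 has HI titre measured at Visit 1 and again after each dose. Neither predictor list names the baseline titre. Section 9.3 does not say after which dose the predictor outcome is taken.

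**The concern.** The stated purpose of these models (abstract; section 1.4) is to help optimise the timing of vaccination. Three features work against that.

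- **Too many terms for the events.** With very few events per variable, ordinary maximum likelihood pushes odds ratios away from 1 and makes them unstable. Total lymphocytes largely contain the B, T and NK counts, so the collinearity is built in.
- **Baseline titre not named.** Whether a child seroconverts depends partly on the starting titre. If age or immune markers track earlier exposure to influenza, their coefficients can absorb its effect.
- **Outcome time point open.** Children aged 9 or over are scheduled for two doses and children under 9 for three. A response taken after the last dose therefore ties dose number to age.

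What is at stake is exaggerated or false predictors being carried into advice on when to vaccinate.

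**Working it through.** **The protocol's own figures.** It gives no event count or precision for the predictor models. Its only calculation is the McNemar power in section 9.2. Using power = Φ[(d√n − 1.96√π) / √(π − d²)], where π is the discordant proportion and d the difference, the four stated cases give 0.798, 0.803, 0.901 and 0.900, against the stated 0.80, 0.80, 0.90 and 0.90. Those figures reproduce, and they do not bear on the regression models.

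**Counting candidates**
- Age, sex: 2
- Diagnosis and treatment: 1–2
- Total lymphocytes, B, CD4, CD8, NK: 5
- Memory T, memory B: 2
- IgG, IgA, IgM: 3
- Total: 13–14, before any multi-level factor is coded.

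**Events per variable** = smaller outcome class ÷ number of variables.

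| n | Seroconversion | Smaller class | Per variable (14) | Per variable (13) |
|---|---|---|---|---|
| 80 | 33% | 26.4 | 1.9 | 2.0 |
| 80 | 43% | 34.4 | 2.5 | 2.6 |
| 80 | 50% (best case) | 40 | 2.9 | 3.1 |
| 60 | 33% | 19.8 | 1.4 | 1.5 |
| 60 | 43% | 25.8 | 1.8 | 2.0 |

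The all-strain model cannot have more events than the weakest strain: at most 26 at 33%. If the joint rate were 10–15% (assumed), there would be 8–12 events, or 0.6–0.9 per variable. The vaccines in section 6.1 are quadrivalent, so there are 4 + 1 = 5 logistic models. The linear models have no events to count; they have 80/14 = 5.7 participants per variable.

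**Consequence, by simulation.** The inputs are assumed: 14 standardised predictors, pairwise correlation 0.3, one true odds ratio of 2.0 and 13 null predictors, with event rates of 33% and 43%.

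| Fit | n | Median estimated OR |
|---|---|---|
| Maximum likelihood | 80 | about 2.35–2.5 |
| Maximum likelihood | 60 | 2.6–2.7 |
| Firth | 80 | about 1.9–2.0 |
| Maximum likelihood, 3 predictors | 80 | 2.1 |

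A second set-up (correlation 0.4, two true log odds ratios of 0.5) gave a mean estimate of about 0.70 at n=80, with 34–37% power for each true predictor.

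**False predictors.** Under maximum likelihood, at least one null variable reaches 5% significance in about 55% of models at n=80. Thirteen independent tests alone give 1 − 0.95¹³ = 49%, and the simulation at n=1000 gives 47–51%. Most of this is therefore multiplicity, with sparse data adding only a little.

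**Age and dose.** By section 5.3, Visit 3 follows two doses in both age groups, because children under 9 give that sample before their third dose. Visit 4, for children under 9 only, follows the third. Dose number therefore steps at age 9 in an analysis of last-dose response, and is constant in an analysis at Visit 3.

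**The case against.** The best defence is that the protocol leaves room. Both predictor lists are open-ended, section 9.3 speaks only of clinically relevant variables, and the final covariate set, variable reduction and penalisation are normally settled in an analysis plan, which is not at hand. Section 9.1 on its own names about nine items; reaching 13–14 needs the cell types and immunoglobulins counted as they are measured. Simultaneous entry of every component by ordinary maximum likelihood is the natural reading of a multivariate logistic regression, but it is not spelled out.

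Much of this stands, and it rules out some stronger readings:

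- A reader might infer that baseline titre is excluded from the models. The documents show only that it is not named.
- A reader might infer that the age effect simply is the dose effect. That does not follow. The outcome time point is not fixed, age still varies within each dose group, and children aged 6–35 months receive the third dose only if the run-in supports it.
- A reader might blame the roughly even chance of a false predictor on sparse data. It is mostly the number of tests.

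What the defence does not remove is the overload. Section 2.2.2 commits the long list to a single multivariate analysis, and no seroconversion rate can lift the smaller class above 40 of 80.

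**Conclusion.** The point holds for the secondary predictor analysis, and the sponsor should act on it. The ceiling of 2.9 events per variable needs only n=80 and 14 variables (3.1 with 13). The range 1.9–2.5 also assumes that rates from an earlier trivalent study apply here and that all 80 children are evaluable. The inflation of an odds ratio of 2.0 to about 2.35–2.5 (n=80) or 2.6–2.7 (n=60) rests on the simulated correlation and on a joint maximum-likelihood fit.

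The absence of baseline titre from the named predictors is a gap worth closing, not proof of omission. The mixing of age with dose number is conditional on a last-dose outcome. The results are likely, rather than certain, to be unreliable. The primary McNemar comparison is untouched.

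**What to change.** Amend section 9.3, and the lists in 2.2.2 and 9.1, to state:

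1. Logistic models are fitted with Firth or ridge penalisation.
2. Total lymphocytes are dropped wherever their subsets are included.
3. The log2 baseline HI titre for the strain is a covariate in each humoral response model, and baseline IFN-γ in the cellular model.
4. The main predictor outcome is taken at Visit 3, when both age groups have had two doses. Response after a third dose is modelled only in children under 9.
5. The linear model of log titre is the main predictor analysis.
6. Predictors are reported as exploratory, with the number of tests stated.

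Steps 2 and 3 leave the variable count unchanged (14 − 1 + 1 = 14), so the relief from sparse data comes from penalisation and from leading with the continuous outcome.

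The cost is wording only, since every measurement is already scheduled. The downsides are that estimates are shrunk and that prediction after a third dose is limited to children under 9. Visit 3 equalises the number of doses but not the antigen content, which section 6.1 gives as 7.5 µg per strain under 3 years and 15 µg from 3 years; the report should say so when interpreting age.

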### **3.8 Duration of study**

The duration of the study is defined as a 24-month study period, starting on 2nd February 2020 and finishing on 31st January 2022.

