## **6.0 VACCINE**

### **6.1 Influenza vaccine**

The influenza vaccine used during the study period will be subject to seasonal recommendations set by the ATAGI, the Australian Influenza Vaccine Committee (AIVC), and the World Health Organization (WHO). All vaccines must be registered by the Therapeutic Goods Administration (TGA) to meet eligibility criteria set by the Australian Department of Health.

Currently, the following vaccines are recommended:

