#### **FluQuadri**

For children aged  $\geq 3$  years  
Administration route: intramuscular injection  
Sponsor: Sanofi-Aventis Australia  
Quadrivalent inactivated influenza vaccine  
Each 0.5 mL pre-filled syringe contains:  
15  $\mu$ g hemagglutinin for each of the 4 recommended influenza virus strains  
 $\leq 100$   $\mu$ g formaldehyde

≤250 µg octoxinol 9

≤1 µg ovalbumin

Annual influenza vaccination is recommended before the influenza season starts. Influenza community circulation usually peaks between June and September in most parts of Australia. The influenza vaccine usually becomes available in March or April of each year.

If more than one influenza vaccine is recommended, these should be administered 4 weeks apart. The first vaccine should be administered as soon as it becomes available to ensure that there is enough time to receive the second (and third dose) before influenza circulation peaks.

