## **7.0 LABORATORY EVALUATIONS**

### **7.1 Assessment of humoral response to influenza vaccine**

Blood samples obtained for the purpose of the humoral response to the influenza vaccine assessment will be centrifuged and sera stored at -80°C. At the end of the influenza season, predicted to be in October, the samples will be sent to the Victorian Infectious Diseases Reference Laboratory (VIDRL) at the Peter Doherty

Institute for Infection and Immunity in Melbourne, Victoria. This centre is a WHO Collaborating Centre for Reference and Research on Influenza and is part of the WHO Global Influenza Surveillance Network organisation (WHO GISN).

HI antibody titers against each vaccine strain will be measured in each sample by standardised assay developed and updated by the WHO GISN (39).

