## **9.0 STATISTICS**

### **9.1 Statistical design**

This is a non-randomised open label study of influenza vaccine response to an enhanced immunisation schedule in a population of paediatric patients treated for cancer.

The primary aim will be to assess the within-patient differences in immune response after repeat doses of the inactivated influenza vaccine in children and adolescents who are being treated for cancer: for those  $\geq 9$  years of age comparing two doses to one dose, and for those  $< 9$  years of age comparing three doses to two doses.

Two separate methods of immune response evaluation will be assessed:

1. The humoral response will be assessed by measuring HI antibodies in participants' sera produced by stimulated B-lymphocytes in response to the influenza vaccine.
2. The cellular response will be assessed by measuring INF- $\gamma$  produced by stimulated T-lymphocytes *in vitro* in response to an influenza vaccine concentrate.

One of the secondary aims will be to assess variables predictive of influenza vaccine immune response. The variables will include participant age, sex, type of disease/treatment and parameters of baseline immune function including total lymphocyte count, B-cell and T-cell count, NK cell count, memory cell count and immunoglobulin levels.

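### The study spans two vaccine seasons, but the secondary predictor models in 9.3 have no season term; adding one is a cheap safeguard.

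*Protocol*

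**What the plan says.** Four parts of the protocol matter.

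- **Two seasons.** Section 3.8: "The duration of the study is defined as a 24-month study period", from 2 February 2020 to 31 January 2022. Section 3.7: "It is estimated that 80 subjects will be recruited over the study period". Section 6.1: "The influenza vaccine usually becomes available in March or April of each year". The period therefore takes in the 2020 and 2021 vaccine supplies.
- **Season-specific vaccine.** Section 6.1: "The influenza vaccine used during the study period will be subject to seasonal recommendations set by the ATAGI", together with the other advisory bodies named there.
- **Season-end serology.** Section 7.1: "At the end of the influenza season, predicted to be in October, the samples will be sent" to the reference laboratory. Section 10.2 repeats this.
- **Predictors.** Section 9.1: "The variables will include participant age, sex, type of disease/treatment and parameters of baseline immune function". Section 2.2.2 gives much the same list. Section 9.3 describes the logistic predictors as demographic and immunological, and those of the linear models simply as clinically relevant. The logistic outcomes are to "predict seroconversion to each influenza vaccine strain and complete seroconversion to all strains of the vaccine". Section 9 does not mention season, vaccine year or assay run.

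**The concern.** The predictor models compare different children, some vaccinated in 2020 and some in 2021. Whatever separates the two seasons, such as the antigens in the vaccine or the level at which the assay reads, forms part of the outcome. If a predictor is also more common in one season, a model without season credits the predictor with some of that difference.

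Two design features could produce such an imbalance. Section 8.3.4 delays the three-dose schedule at 6–35 months until six children aged 3 to under 9 years have had a third dose and the DSMB has advised. Section 3.7 says of the recruitment estimate: "This is based on the incidence and prevalence of patients receiving diagnosis and treatment for cancer". The first season may therefore hold more of the existing patient pool and the second more new diagnoses. Both are inferences.

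The wording of the strain outcomes also assumes a single vaccine. If a strain is replaced between seasons, the protocol does not say whether both antigens are analysed under one label.

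What is at stake is secondary. Section 1.4 intends the predictor results to help optimise the timing of vaccination, and a season artefact could be carried into that advice.

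**Working it through.** **The plan's own figures.** Section 9.2 uses a McNemar test. With discordance p and difference d, N = [1.960·√p + z(power)·√(p − d²)]² / d² (two-sided α = 0.05). For p = 0.15, d = 0.12 and 80% power: [1.960·√0.15 + 0.842·√0.1356]² / 0.0144 = 79.4, against a stated 80. The other three scenarios give 60.3, 59.9 and 79.9, against 60, 60 and 80. The figures reproduce. Each child is its own control, normally within one season, so a season term changes none of them.

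**Inputs for the predictor models.** From the documents: N = 80 (3.7) and two seasons (3.8, 6.1). Assumed, because the documents give no figure: 40 children per season, no true predictor effect, SD of log2 titre 1.5 to 2.0, and the season shifts and predictor shares below.

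**Log titre.** The bias from omitting season is shift × cov(X,S)/var(X). Take a predictor share of 30% in one season and 60% in the other:

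- cov(X,S) = 0.25 × (0.60 − 0.30) = 0.075
- var(X) = 0.45 × 0.55 = 0.2475
- ratio = 0.303
- twofold shift (1 log2 unit): bias 0.303, and 2^0.303 = 1.23
- fourfold shift (2 log2 units): bias 0.606, and 2^0.606 ≈ 1.52

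Simulated false-positive rates at a nominal 5%:

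| Predictor share | Twofold shift | Fourfold shift | With season term |
|---|---|---|---|
| 50% / 50% | 5% | 5% | 5% |
| 40% / 60% | 7–9% | 13–17% | 5% |
| 30% / 60% | 10–14% | 22–33% | 5% |

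**Seroconversion.** Let r1 and r2 be the season rates, and let the predictor share be 70% and 30%. Rates of 43% and 33% both appear in 1.3, as rates for different strains in the earlier local study; here they only set a scale. Rate with the predictor: 0.7 × 0.43 + 0.3 × 0.33 = 0.400. Rate without it: 0.3 × 0.43 + 0.7 × 0.33 = 0.360. Spurious OR = (0.400/0.600)/(0.360/0.640) = 1.19. Repeating this for other rates and shares, with simulated false-positive rates:

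| Season rates | 50/50 | 60/40 | 70/30 |
|---|---|---|---|
| 43% vs 33% | OR 1.00, 5% | OR 1.09, 5% | OR 1.19, 6% |
| 43% vs 23% | OR 1.00, 5% | OR 1.20, 7% | OR 1.44, 11% |
| 55% vs 30% | OR 1.00, 5% | OR 1.23, 8% | OR 1.51, 14% |

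With a season term the rate is 4–6% in every row.

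**Where a laboratory-run shift cancels.** If a run multiplies all of a child's titres by c, the fold rise is (c·post)/(c·pre) = post/pre. The geometric mean fold increase (GMFI) is unchanged when the child's sera share a run, which season-end shipment makes likely. The fourfold part of the seroconversion definition in 1.3 cancels in the same way; the rule of below 10 rising to at least 40 does not. A run shift therefore acts mainly on absolute log titre. A true strain difference can still act on seroconversion.

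**Gain without imbalance.** A twofold shift adds 0.25 × 1² to the residual variance when season is omitted. Residual SD is then √(2.25 + 0.25) = 1.58 rather than 1.50, or √(4 + 0.25) = 2.06 rather than 2.00. The season term removes this.

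**The case against.** The strongest reply is that this is a silence of the kind a statistical analysis plan normally fills. The list in 9.1 says what the variables will include, which leaves it open. That limits the finding but does not remove it: 9.3 describes the logistic predictors as demographic and immunological, and season is neither, so a model fitted as written would omit it.

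A reader might infer several stronger things that the documents do not support:

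- *That the seasons are pooled by design, or that a strain or assay level changes.* No sentence says so. Seasonal recommendations and season-end shipment make a change possible, no more. Section 7.1 measures titres against each vaccine strain, and the natural reading of a strain is the one in the vaccine the child received.
- *That GMFI is distorted by laboratory run.* It is a within-child ratio, so a shared run shift cancels. No between-child test of pooled GMT or GMFI is planned.
- *That the run-in pushes the youngest children into the second year.* With visits 4–6 weeks apart (5.2), a third dose falls 8–12 weeks after the first. With vaccine from March or April, the gate could open between about May and July of the first season. It also withholds only the third dose.
- *That the false-positive rate is known to be inflated.* It needs both a season shift and a different predictor mix. A 10-point seroconversion gap has almost no effect even at 70/30.

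**Conclusion.** The point stands as a low-severity improvement to a secondary analysis. It is not a demonstrated error. The protocol covers two seasons with season-specific vaccine and season-end serology, and the predictor models in 9.3 are described without season. Confounding is possible, mainly in the models of absolute log titre and, through true strain differences, in the seroconversion models.

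Its size depends wholly on the assumed shift and imbalance. It runs from nothing with a balanced mix, through a spurious GMT ratio of about 1.23 with 10–14% false positives (twofold shift, 30% vs 60%), to higher figures only under a fourfold shift. The primary McNemar comparison and the sample size are untouched.

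**What to change.** In 9.3:

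1. Add season (2020 vs 2021, from the vaccination date) as a fixed term in every logistic and linear predictor model.
2. Define each strain as the strain in the vaccine that the child received.
3. Where a strain changed between seasons, report GMT, GMFI, seroprotection and seroconversion for it by season, beside any pooled figure.

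This takes two or three sentences and no new data. It costs one degree of freedom per model and wider intervals in the season-specific tables. If a predictor turns out to be strongly tied to season, its adjusted estimate will also be less precise, which correctly reflects what the data can separate.
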